## Abstract

**Background:**

Heart failure (HF) is the leading cause of mortality, morbidity, and rehospitalization in Appalachia. Rural areas have the highest HF mortality rates. Rural Appalachians lack access to health services and end-of-life palliative care (EOLPC) and have extreme inequities in health.

**Methods:**

The aim of this mixed methods randomized controlled trial (RCT) is to test the integrated nurse-led intervention bundle of the HF home EOLPC (**HF**-FamPAL**home**CARE) and to assess its ability to maintain sustainability with rural stakeholders, visiting volunteers, and the WV Faith Community Nurse Network. The participants are adult patients (50 to 80 years) with HF (NYHA III and IV and Stages C and D) and their caregivers (≥ 45 to 80 years).

The primary aim is to test the outcomes of patients with HF and family caregivers (104 dyads) managing home supportive EOLPC in rural WV. The secondary aim is to assess the bundled intervention for helpfulness, cost and sustainability. All participants received standard care from their regular providers. The intervention group received 2 home visits, 3 biweekly telephone calls and telephone reinforcement across 12 months. Data collection for both groups was conducted at baseline and at 3, 6, 9, and 12 months.

**Discussion:**

This RCT supports research to improve health equity by improving access to health services and addressing social determinants of health in underrepresented rural Appalachia. It is designed to test practical, sustainable approaches using available local resources to address HF symptom management, support EOLPC preferences, support older adults’ functional health and HF home caregiving skills, and provide social support.

**Trial Registration:**

ClinicalTrials.gov NCT06791850 Registered on date 19 January 2025.

## Background

Heart failure (HF) affects nearly 8 million Americans [1] and is increasing at a rate of 46%, with escalating costs of up to $70 billion annually [2]. HF is the leading cause of mortality, morbidity, and rehospitalization in Appalachia [3]. Rural areas have the highest HF mortality rates [4]. West Virginia (WV), the only state totally within the Appalachian region, has the highest HF death rate in the U.S. (32.6 per 100,000), with the greatest number of deaths occurring in those over age 65 [5]. HF is devastating for patients and their family caregivers, especially during the end stages [6]. Families are unprepared for this deteriorating condition, the burden of home caregiving, and the fear of painful death [7]. In addition, rural Appalachians lack access to health services and end-of-life palliative care (EOLPC) [8] and experience extreme health inequities [9]. Furthermore, physical and social isolation [10] is common due to the lack of/difficulty with transportation in WV’s rural mountainous environment, with limited internet or cellular services [9].

The goals of palliative care are to prevent and alleviate suffering and to enhance the quality of life for both patients and their families through a team-based, patient-focused approach to managing the discomfort, symptoms, and stresses associated with serious illnesses. This is achieved through accurate assessment, identification, and referral and through the treatment of pain and other symptoms, whether they are physical, psychological, or spiritual [11].

This RCT addresses the National Institutes of Nursing Research (NINR) strategic initiatives to identify ways to improve health outcomes and health equity in rural areas [12]. It also addresses the goals of the National Palliative Care Research Cooperative (PCRC) [13] and the EOLPC priorities of national organizations in advocating for the nursing community and for patients, families, and caregivers across all aspects of heart failure care [14].

Our preliminary RCT enrolled patients with HF and their family caregivers (N = 78) in the family palliative care (FamPALcare) preliminary trial. Compared with controls, both patients and their family caregivers had significant improvements in health measures and EOLPC outcomes at 6 months [15]. Additionally, the PI’s recent project, ‘Appalachian Visiting Neighbors,’ was tested with 30 older adults living alone. The results revealed that these older adults were able to improve their functional health by the 3-month follow-up. Both interventions were empirically verified as feasible and sustainable [16]. For both studies, Appalachian faith community nurses and trained visiting volunteers implemented all intervention visits and reinforced follow-up telephone calls. In practice, these nurses coordinated access and free travel to regional health care.

Thus, this RCT aims to test the integrated nurse-led intervention bundle of 1) HF home palliative care (**HF**-FamPAL**home**CARE), 2) visiting volunteers, and 3) Appalachian faith community nurses. This intervention bundle aims to address rural disparities in access to health care with the help of faith community nurses and local visiting volunteers [17, 18]. The intervention bundle components began with a series of preliminary studies while collaborating with Appalachian rural, religious, and policy leaders on our Rural Stakeholders Advisory Board. Our intervention’s bundle components are designed to mitigate Appalachian health disparities [19] by addressing critical social determinants of health (SDoH), such as faith community nurses reducing costs by enabling direct access to available health services, utilizing clearly illustrated HF home care guides for low literacy [20], and inspecting for safe housing for older adults [21].

## Conceptual framework guiding the HF-FamPALhomeCARE in this RCT

This RCT is guided by the social support conceptual theory confirmed by conceptual reviews and meta-analyses [22, 23]. Social support, such as helping neighbors, is a tenet of rural Appalachian culture [24]. This framework consists of four social support constructs, including emotional, informational, instrumental, and affiliation support [25]. Emotional support is described as providing caring listening, which can help decrease depression/anxiety [26]. Informational support is the process of knowledge transfer, which includes providing health information and instruction on specific HF home caregiving skills [25]. Instrumental support improves the in-home family caregiving burden by providing access to health care through the WV Faith Community Nurse Network and by organizing assistance [27] with daily needs such as shopping or transportation [28] utilizing local community resources. Affiliation support includes engaging in functional well-being and social activities with visiting volunteers to decrease social isolation [29]. Thus, social support and the intervention components are directly linked to patient and caregiver outcomes.

## Methods/design

### Aims

The aims of this RCT are to test the outcomes of the **HF**-FamPAL**home**CARE bundled intervention, with patients and family caregivers (104 dyads) managing home supportive EOLPC for end-stage HF in rural WV. The specific aims and hypotheses, with outcome measures for this RCT, are listed in Table 1.

**Table 1 Tab1:** Specific Aims, Hypotheses, with the Outcome Measures for this RCT

**Primary Aims** are to test the outcomes of the **HF**-FamPAL**home**CARE bundled intervention, with patients and family caregivers managing home supportive EOLPC for end-stage HF in rural WV
**Aim 1:** Compared to the control group at 3, 6, 9 months, and 1-year follow-up:
***Hypothesis 1a.*** The patients in the intervention group will have higher scores on HF-related health quality-of-life measure and on the functional health well-being scale
***Hypothesis 1b.*** The family caregivers in the intervention group will have higher scores on the functional health well-being scale
**Aim 2:** Compared to the control group at 3, 6, 9 months, and 1-year follow-up:
***Hypothesis 2a.*** The patients in the intervention group will have (a) lower depression and anxiety scores and (b) higher numbers of signed EOL advance directives
***Hypothesis 2b.*** The family caregivers in the intervention group will have (a) lower depression and anxiety scores, (b) lower home caregiving burden scores, and (c) improved home HF EOLPC preparedness and improved home palliative care scores
**Secondary Aim** (Aim 3) is to assess the bundled intervention helpfulness, cost, and the plans for maintaining the sustainability of our faith community nurses and visiting volunteers engagement across rural WV
***Aim 3a.*** Compare the bundled intervention helpfulness questionnaire ratings by the patient, family caregiver intervention group participants, and the interventionists (faith community nurse and visiting volunteers). Determine the implementation cost of the **HF**-FamPAL**home**CARE bundle
***Aim 3b.*** Using focus group research, determine 10-year plans for sustaining the bundle implementation, maintaining rural volunteers and coordinating administrative aspects of the program

### Design/methodology

This study uses a randomized controlled trial (RCT) design stratified by sex to determine the effectiveness and helpfulness of the **HF**-FamPAL**home**CARE bundled intervention (N = 208, 104 dyads: 104 patients and 104 family caregivers). The intervention group (52 dyads) will receive the intervention. The control group (52 dyads) will receive attention control consisting of education on general health topics that indirectly affect HF (e.g., vaccinations, handwashing). At the end of the 12-month completion period, each group received the content provided to the other group. See Fig. 1.

**Fig. 1 Fig1:**
[figure not shown]
HF-FamPALhomeCARE Coaching Intervention (X_1_ to X_9_) Sequence with Data Collection (O_1_–O_5_)

#### Randomization

The consulting statistician will use computerized randomization to generate numbers for subject enrollment. Two separate randomization lists will be created: one for males and one for females. Families will then be randomly assigned to either the control or intervention group at a 1:1 ratio. The group assignments are placed in sealed envelopes according to sex. Our RCT design adheres to CONSORT standards and rigorous research procedures [30]. The study is designed to enhance both internal and external validity, making it suitable for detecting differences between groups in behavioral intervention trials [31].

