#### Characteristics of the participants

Adult patients (50 to 80 years of age) with HF (NYHA III and IV and Stages C and D) and their caregivers (≥ 45 to 80 years of age) who are involved in daily home care will be recruited. Recent national statistics revealed that 34% of adults aged 50 years or above had Stage B HF, which progresses to end-stages C and D within 5 years [32]. The inclusion age range for patients (50 to 80 years of age) is scientifically justified based on the 2023 National Heart Failure statistics from the American Heart Association (Chapter 22) [1] and our recent population-based heart failure study using 37,872 HF patients seen at WVU hospitals between 2008 and 2020 [33]. The rationale for the caregiver age range is based on our recent caregiving RCT study in Rural Appalachia [15] and two systematic reviews [6, 34] that included a total of 74 studies. These studies reported that the majority of caregivers’ ages ranged from 45 to 80 years.

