#### Sample size

The power and sample size determination is based on a preliminary RCT, which revealed a moderate effect reduction in the burden of caregiving and improvements in patients’ HF-related health status [15]. With the use of G*Power v.3.1.9.7 for repeated-measures ANOVA with α = 0.05, Cohen’s d = 0.25 (moderate effect size), a power of 80%, two groups with 5 measurements, and correlations among repeated measures (0.50), a *sample size of 86 family dyads* will be needed. Our power analyses performed by this study’s statistician indicate that this sample size is sensitive enough to detect a significant difference in the study outcomes with this repeated measure design [36].

Our biostatistician’s revised precision calculation for linear mixed model analysis was based on the effect size outcomes of our HF palliative care studies. To account for an expected 20% attrition (many due to HF-related deaths), eight additional families will be recruited for each group. The calculated sample size was 86 patients, with an additional n = 18 for the expected 20% attrition rate (total sample N = 208; 104 patients and 104 caregivers) for this study. In this analysis, the random and fixed effects and quarterly repeated measures also add power.

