## Limitations and alternatives

The population of West Virginia is 93% Caucasian, but we have successfully enrolled underrepresented minorities in past studies. We anticipate a 20% attrition rate, primarily due to HF-related deaths. In previous studies, few caregivers withdrew after patient death, indicating that they were able to contact study nurses. To increase enrollment, program brochures are distributed in local churches by lay ministers and faith community nurses. Additionally, healthcare providers involved in HF patient discharges or ER visits may refer families to the program. Finally, the West Virginia University (WVU) integrated data repository (IDR) will be used for enrollment, as it has proven helpful for screening patients with HF across WV counties in the PI’s previous trials.

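### The stated Aim 1 and 2 model names neither sex, the only stratification factor, nor NYHA class, known at screening; adding both would gain a little precision

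*Protocol article*

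**What the plan says.** Under Design/methodology the trial is a "randomized controlled trial (RCT) design stratified by sex". The Randomization section repeats this: "Two separate randomization lists will be created: one for males and one for females", and then "Families will then be randomly assigned to either the control or intervention group at a 1:1 ratio". No other stratification factor is named, and no reason is given for choosing sex.

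The population, under Characteristics of the participants, is "Adult patients (50 to 80 years of age) with HF (NYHA III and IV and Stages C and D". NYHA class therefore has to be established at screening. Under Limitations and alternatives the authors write "We anticipate a 20% attrition rate, primarily due to HF-related deaths". The planned size, under Sample size, is "total sample N = 208; 104 patients and 104 caregivers", which gives 52 dyads per arm.

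The section Data analysis for Aims 1 & 2 lists three fixed terms (arm, time and their interaction), with random effects for patient and caregiver. Sex and severity are not among the terms named. The section on data management foresees a check of baseline comparability but gives no rule for adjustment.

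**The concern.** Severity is the baseline characteristic most likely to affect heart-failure quality of life, functional health and survival. That is a clinical assumption which the protocol does not state, although naming heart-failure death as the main cause of attrition points the same way. It is recorded before allocation, yet as described neither the design nor the model uses it. The model also omits the one factor that was used to stratify.

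Two things are at stake. The first is precision: variation explained by NYHA class stays in the error term of any between-group comparison at follow-up. The second is the reading of the realised result. If the arms happen to differ in their share of class IV patients, part of the observed difference reflects case mix, and any adjustment decided after seeing the imbalance would be open to challenge.

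**Working it through.** The plan gives no figure for imbalance or for the effect of severity, so there is none to reproduce. From the document come the 104 dyads in two arms of 52, the single stratum factor, the three named fixed terms and the 20% attrition. Assumed, because the documents are silent: a class IV share of 20 to 50%, an outcome gap between class IV and class III of 0.3 to 0.8 SD, and loss of 10 to 15% in class III against 30 to 35% in class IV.

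**1. How often the arms differ.** With K class IV patients among 104 split 52/52 (sex strata ignored), the number X in one arm is hypergeometric and the difference in shares is (2X − K)/52.

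| Class IV share (K) | SD of difference | P(gap ≥ 10 points) | P(gap ≥ 15 points) | P(gap ≥ 20 points) |
|---|---|---|---|---|
| 20% (21) | 7.9 points | 14% | 5% | 1% |
| 30% (31) | 9.0 points | 20% | 9% | 3% |
| 40% (42) | 9.7 points | 32% | 16% | 3% |
| 50% (52) | 9.9 points | 33% | 17% | 3% |

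A moderate imbalance is quite possible; a large one is rare.

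**2. What a 15-point gap does to the estimate.** Shift = gap × severity effect: 0.15 × 0.3 = 0.045 SD; 0.15 × 0.5 = 0.075 SD; 0.15 × 0.8 = 0.12 SD. The standard error of an unadjusted comparison at one visit with 52 per arm is √(2/52) = 0.196 SD. The shift is therefore 0.045/0.196 = 0.23 to 0.12/0.196 = 0.61 of a standard error.

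**3. What it does to loss.** Shift = gap × difference in loss: 0.15 × (0.30 − 0.15) = 2.3 points; 0.15 × (0.30 − 0.12) = 2.7 points; 0.15 × (0.35 − 0.10) = 3.8 points. Chance alone gives the between-arm difference in loss an SD of √(2 × 0.2 × 0.8/52) = 7.8 points.

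**4. Bias and error rate.** One visit was simulated with 104 patients, 40% in class IV, loss of 13% in class III and 30% in class IV, sex-only lists in blocks of four (the blocks are an assumption), and 6,000 runs per scenario. Without adjustment the mean estimate was −0.003 to 0.001 when the true effect was zero, and 0.500 to 0.503 when it was 0.5 SD. Type I error was 5.4 to 5.6%, about nominal.

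**5. What adjustment for NYHA class gains.** From the same simulation with a true effect of 0.5 SD:

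| Severity effect | SD, unadjusted | SD, adjusted | Reduction | Power, unadjusted | Power, adjusted |
|---|---|---|---|---|---|
| 0.5 SD | 0.2188 | 0.2127 | 2.8% | 62% | 64% |
| 0.8 SD | 0.2181 | 0.2035 | 6.7% | 63% | 69% |

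A closed form agrees. With total variance 1, adjustment multiplies the SD by √(1 − e²p(1 − p)). At p = 0.4 this is √(1 − 0.06) = 0.970 for e = 0.5 and √(1 − 0.154) = 0.920 for e = 0.8, that is, reductions of 3% and 8%. At e = 0.3 it is √(1 − 0.022) = 0.989, about 1%.

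A repeated-measures simulation (30% class IV, severity effect 0.5 to 0.8 SD, NYHA-dependent loss) gives reductions of about 2 to 4% for the 12-month group contrast, 3 to 8% for the contrast averaged over follow-up, and essentially none for change from baseline. The last result is expected: a severity effect that is constant over time cancels when baseline is subtracted.

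**6. Stratifying by NYHA class instead.** With a true effect of 0.5 SD, lists by sex and class with no adjustment gave SDs of 0.215 (severity effect 0.5) and 0.203 (severity effect 0.8). That is close to what sex-only lists achieve with adjustment (0.213 and 0.204).

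**The case against.** The strongest reply is that nothing here is an error. Sex-only stratification is a legitimate choice for 104 dyads, the two places that describe it agree, and the document assigns a prognostic role to neither sex nor NYHA class. That stands, and for that reason the point is an improvement to the model and not a fault in the randomisation.

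A reader might infer that mixing class III and IV without stratifying biases the patient outcomes. The documents do not support this. Allocation is random, the estimate is unbiased over repeated randomisation, and the test level and confidence interval already allow for chance imbalance. A reader might also infer that severity imbalance will produce materially different loss between arms. A 15-point gap moves expected loss by 2.3 to 3.8 points, well inside the 7.8-point SD that chance produces anyway.

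Two further replies have force. Baseline is one of the five measurements, so treatment-by-time contrasts already remove at least part of a starting gap; this limits the benefit to between-group contrasts at follow-up. And the article says what the models will include without saying that they include nothing else, so the unseen analysis plan may list covariates. That lowers the weight of the point, but it remains useful to have the terms fixed before the data are seen.

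**Conclusion.** The point holds as a minor matter of precision. As described, the model leaves out both the stratification factor and a plausible severity covariate that every patient has at screening. The consequence is somewhat more variance than necessary and a realised estimate that can move by about 0.05 to 0.12 SD with a 15-point NYHA gap in an unadjusted single-visit comparison.

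Adjustment would lower the SD of follow-up contrasts by roughly 2 to 8% for a severity effect of 0.5 to 0.8 SD (about 1% for 0.3 SD), with little or no gain for change from baseline. All these sizes rest on an assumed NYHA mix and severity effect that the documents do not give. They do not support a claim of bias, of invalid randomisation, or of a need to change the sample size.

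**What to change.** Keep the two sex lists. State in the analysis plan, before outcome data are examined, that every Aim 1 and Aim 2 model includes the patient's NYHA class at screening (III or IV) and sex as fixed effects, besides arm, time and their interaction. Say whether sex means the patient's or the caregiver's, since the Randomization section does not; the model term should match the one used for the lists. If the analysis plan already contains these terms, no change is needed.

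The cost is one or two model terms from data already in hand, with no new data collection and no change in sample size. Adding NYHA class as a second stratum is possible but not needed. It risks a thin class IV stratum, balances the arms only if allocation within each list is blocked or otherwise restricted (which the article does not describe), and gains little over adjustment.

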#### Characteristics of the participants

Adult patients (50 to 80 years of age) with HF (NYHA III and IV and Stages C and D) and their caregivers (≥ 45 to 80 years of age) who are involved in daily home care will be recruited. Recent national statistics revealed that 34% of adults aged 50 years or above had Stage B HF, which progresses to end-stages C and D within 5 years [32]. The inclusion age range for patients (50 to 80 years of age) is scientifically justified based on the 2023 National Heart Failure statistics from the American Heart Association (Chapter 22) [1] and our recent population-based heart failure study using 37,872 HF patients seen at WVU hospitals between 2008 and 2020 [33]. The rationale for the caregiver age range is based on our recent caregiving RCT study in Rural Appalachia [15] and two systematic reviews [6, 34] that included a total of 74 studies. These studies reported that the majority of caregivers’ ages ranged from 45 to 80 years.

#### Eligibility criteria

Patients will meet the inclusion criteria if they have advanced systolic and/or diastolic HF and have an informal caregiver aged 45 to 80. They do not need to live in the same home. Cardiology consultants specify the inclusion of patients with both systolic and diastolic dysfunction, as both require similar HF home care management regimens and have advanced EOL symptoms and palliative care needs [14]. Caregivers are those designated by the HF patient as a nonpaid primary person who assists with HF home care, thus not requiring caregivers to be spouses. All participants must be cognitively intact, able to provide written consent, and able to read and write in English. Each patient and his or her caregiver will be randomly assigned to a study group as a dyad.

Patients will be excluded if they have received or are on a waiting list for a heart transplant, have a left ventricular assist device, or have another terminal illness or dementia. Caregivers will be excluded if they have a disability that precludes their use of **HF**-FamPAL**home**Care intervention materials such as dementia [35].

